|                                                                          | hypercapnic) and the type of patients (surgical, respiratory, burned, cardiovascular), on the results of the main outcome.                                                                                                                                                                                                                                                                                                                                                                                                                                                                                                                                                                                                                                                                                                                                                                                                                                                                       |
| NUMBER OF SUBJECTS                                                | 37 for each group and 74 in total.                                                                                                                                                                                                                                                                                                                                                                                                                                                                                                                                                                                                                                                                                                                                                                                                                                                                                                                                                               |

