There are several moments when tongue function can be affected by mechanical ventilation. From the moment of endotracheal tube insertion with a laryngoscope that compresses and deviates the tongue during the procedure, lingual nerve injuries can occur, resulting in loss of sensation. Additionally, immobilization or reduced frequency and range of tongue movement during intubation can decrease its contractile strength. (10,15,16) It has been shown that somatosensory and motor impairment of the tongue occurs regardless of age, sex, smoking history, and patient comorbidities. Compared to a control group, the decrease in strength was more persistent than sensory alteration, which has shown at least partial improvement within 14 days post-extubation. (15)

Post-extubation dysphagia is associated with delayed resumption of oral intake, potentially increasing the risks of dehydration and malnutrition in patients who are often in hypercatabolic processes, which is particularly important in the elderly population, who are often frail and have limited functional reserve. (1,9) Other factors associated with swallowing disorders in ICU patients include gastroesophageal reflux and desynchrony between breathing and swallowing processes. (10)

Extubation failure, usually defined as the need for re-intubation within 24-72 hours following planned extubation, leads to a worse prognosis, increased mortality, and hospital stay, and can occur in 2-25% of patients. Causes include swallowing dysfunction, ineffective cough, upper airway obstruction, and excessive secretions in the airway. (17) In a related study of patients in a medical-surgical ICU, intubated for more than 6 days, it was found that the gag reflex is a determinant for extubation failure related to aspiration or excessive secretions in the airway. (17) Both frailty and generalized weakness have been associated with impaired ability to generate an effective cough to expel tracheal material. (1)

The growing concern to minimize the impact of medical interventions on the overall recovery process of patients has led to a cultural shift in ICUs, where it was previously more common to find most patients deeply sedated and on invasive mechanical ventilation, sometimes for prolonged periods, and today, fostering an increasingly conducive environment for rehabilitation. (18)

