### 6.3. Sample size

Based on the study published by Schweickert et al. where they found that the mean number of days of mechanical ventilation in patients with usual physical therapy was  $6.1 \pm 1.4$  days and in early therapy it was  $3.4 \pm 1.25$  days (32), for an alpha error of 0.05 and a statistical power of 0.8 is considered the following formula:

$$ES = \frac{|\mu_1 - \mu_2|}{\sqrt{DE1^2 - DE2^2/2}}$$

$$ES = \frac{|6.1 - 3.4|}{\sqrt{1.40^2 - 1.25^2/2}}$$

$$ES = \frac{2.7}{\sqrt{3.52/2}}$$

$$ES = 2.03$$

With the effect size calculated ( $ES \approx 0.4463$ ), we can use the formula for the sample size mentioned earlier:

$$n = \frac{2 \left( \frac{Z\alpha}{2} + Z\beta \right)^2 \cdot (\sigma_1^2 + \sigma_2^2)}{ES^2}$$

Where  $\frac{Z\alpha}{2}$  is the critical value corresponding to the alpha significance level /2 to  $\alpha = 0.025$ ,  $\frac{Z\alpha}{2} \approx 2.81$

and  $Z\beta$  is the critical value corresponding to the statistical power beta to  $\beta = 0.90$ ,  $Z\beta \approx 1.28$

The other values we have are the same:

- Mean of group 1 ( $\mu_1$ ) = 6.1 days
- Standard deviation of group 1 ( $\sigma_1$ ) = 1.4 days
- Mean of group 2 ( $\mu_2$ ) = 3.4 days
- Standard deviation of group 2 ( $\sigma_2$ ) = 1.25 days

Effect size ( $ES$ )  $\approx 20.03$  (previously calculated)

Substituting these values into the formula:

$$n = \frac{2 (2.81 + 1.28)^2 \cdot ((1.40)^2 + (1.25)^2)}{(2.03)^2}$$

$$n = \frac{2 (4.09)^2 \cdot (1.96 + 1.56)}{4.13}$$

$$n = \frac{2 (16.72) \cdot (3.52)}{4.13}$$

$$n = \frac{(35.35) \cdot (3.52)}{4.14}$$

$$n = 30.29$$

Rounding:

$$n = 31 \text{ by each group}$$

To the estimated 31 patients per arm, an extra 20% (6 patients per arm) is added to minimize the loss of statistical power in case patients withdraw from the study or there are missing data.

The sample size has also been determined based on the magnitude of the expected effect of mobilization within 48-72 hours of mechanical ventilation, as suggested in the reference study (33), which justifies our choice to evaluate early mobilization at 24 hours versus 72 hours after mechanical ventilation in our study.

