#### 6.4. Sampling and Randomization

Patients who meet the inclusion criteria will be assigned, through stratified randomization by sex and age group (under 65 years and over 65 years), to one of the two study groups at a 1:1 ratio (sampling stratified randomized). The number of resulting strata corresponds to 4. Randomization will be applied to each stratum. This type of sampling and randomization reduces possible imbalances and increases statistical power, considering that the number of participants per arm is 37. Allocation concealment will be carried out using sealed and sequentially numbered opaque envelopes, which will be in the Intensive Care Unit office on the fourth floor of the expansion building. A record of the person who opened the envelope will be kept by Good Clinical Practice guidelines.

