Variables that could act as confounding factors will be evaluated through a second multiple regression model. In this model, the potentially confounding variable will be removed, and the resulting slope or estimator (adjusted estimate) will be calculated. If there is a change greater than 15%-20%, the confounding variable will be included in the final model. Otherwise, the most parsimonious model will be chosen.

To evaluate the interaction between two variables, another regression model will be performed, including a new variable resulting from multiplying the two potentially interacting variables. If the regression coefficient of this new variable has a significance level of less than 0.05, it is concluded that there is an interaction, and this variable will be included in the model. Variables with potential interaction will be identified by evaluating confounding factors. Researchers will also evaluate clinical variables that may be considered as interaction or confounding variables through the above-described strategy.

The assumption of proportional hazard will be evaluated using Schoenfeld residuals, and influential values will be analyzed through residuals versus observations plots. Multicollinearity will be assessed through matrix curves.

Logistic regression models will be used to assess the relationship between our dichotomous variables, such as failed extubation, post-extubation NIV, prolonged mechanical ventilation, tracheostomy, and dysphonia, and the other studied variables. The assumptions of a logistic regression model, such as linearity in the log of the odds, independence of errors, homogeneity of variance, absence of multicollinearity, absence of outliers, and proportionality of effects, will be evaluated through residual analysis and graphical diagnostics, such as Pearson residual analysis or deviance residual analysis.

A multiplicity adjustment strategy will be employed in statistical tests, such as the Bonferroni method, Holm-Bonferroni, or other methods that control the false discovery rate (FDR), to maintain the overall type 1 error rate at an acceptable level.

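### Section 6.13 sets logistic models of five yes/no outcomes against about 80 studied variables with no limit by events, and lists two assumptions that binary logistic regression does not make

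*Protocol*

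**What the plan says.** Protocol section 6.13 states that "Logistic regression models will be used to assess the relationship between our dichotomous variables", names failed extubation, post-extubation NIV, prolonged mechanical ventilation, tracheostomy and dysphonia as examples, and sets them against the other variables studied. Section 1 repeats the plan. The variable table in section 6.11 has about 80 entries. Section 6.13 sets no minimum event count and no limit on predictors for these models. It does not name the estimator or say whether predictors enter singly or jointly.

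The same paragraph gives the assumptions to be checked. After linearity in the log odds it lists "independence of errors, homogeneity of variance, absence of multicollinearity, absence of outliers, and proportionality of effects", to be examined through Pearson or deviance residuals and plots.

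The trial size in section 1 is "37 for each group and 74 in total". The only event rate given for any of the five outcomes is in the background (section 4): extubation failure, "usually defined as the need for re-intubation within 24-72 hours following planned extubation", "can occur in 2-25% of patients". Section 6.11 defines the trial's own outcome over 48 hours after removal of the airway.

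Section 6.6 lists extubation failure and need for non-invasive ventilation as secondary outcomes and dysphonia as exploratory. Prolonged ventilation and tracheostomy are not in that list. Section 6.13 separately plans a chi-square or Fisher's exact test for categorical variables between arms.

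**The concern.** What limits a logistic model is the number of events, and 74 patients can yield very few. If one arm has no event, the ordinary odds ratio for arm is zero or infinite; if neither arm has one, it is undefined. When many predictors enter together, some combination of them can split events from non-events by chance, and the fit then has no finite solution. Followed as written, the paragraph permits models that the data cannot support. The odds ratios at risk include those for two secondary outcomes.

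Two further problems do not depend on the event rate. One of the named outcomes is a threshold on another studied variable. And two of the listed assumptions do not belong to the model, so an analyst following the text would be testing for something the method does not require.

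**Working it through.** **Trial size.** Section 6.3: "To the estimated 31 patients per arm, an extra 20% (6 patients per arm) is added". So 31 + 6 = 37 per arm, and with allocation "to one of the two study groups at a 1:1 ratio" the total is 2 × 37 = 74, matching section 1. Without the allowance it is 2 × 31 = 62.

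**Expected failed extubations.** Events = N × p, with p from the 2-25% range; 5% and 10% are intermediate values. Supported parameters = events ÷ 10, where 10 events per parameter is a rule of thumb and not a figure in the protocol.

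**An arm with no event.** With the same rate p in both arms, q = (1 − p)^37 is the chance that one given arm is empty. P(at least one empty) = 1 − (1 − q)². P(both empty) = q². At 2%, q = 0.98^37 = 0.4735, so 1 − 0.5265² = 0.723 and q² = 0.224.

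| Rate p | Events, N = 74 | Events, N = 62 | Parameters at 10 events each (N = 74) | At least one empty arm | Both arms empty |
|---|---|---|---|---|---|
| 2% | 1.48 | 1.24 | 0.15 | 72.3% | 22.4% |
| 5% | 3.70 | 3.10 | 0.37 | 27.7% | 2.2% |
| 10% | 7.40 | 6.20 | 0.74 | 4.0% | 0.04% |
| 25% | 18.5 | 15.5 | 1.85 | 0.005% | about 0 |

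At 2%, the arm odds ratio is zero or infinite in 72.3 − 22.4 = about 50% of trials and undefined in a further 22%.

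**Several predictors entered jointly.** This was simulated with N = 74 and 200 trials per cell. The predictors were arm plus null variables, a mix of 30% binary and normal. Separation was checked by linear programming, and trials with no event at all were counted as failures.

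| Rate | 5 predictors | 10 | 20 | 30 |
|---|---|---|---|---|
| 2% | 92% | 98% | 100% | 100% |
| 10% | 19% | 41% | 73% | 100% (rounded) |
| 25% | 0.5% | 2% | 5% | 53% |

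**Precision when the model can be fitted.** Woolf standard error of the log odds ratio, 37 per arm:
- 9 v 9 events: √(1/9 + 1/28 + 1/9 + 1/28) = 0.542; 95% CI 0.35 to 2.89.
- 1 v 1 event: √(1 + 1/36 + 1 + 1/36) = 1.434; 95% CI 0.06 to 16.6.

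**Outcome defined by a predictor.** Section 6.11 defines prolonged ventilation as invasive ventilation for more than 14 days, and the same table holds days of mechanical ventilation. Every patient above 14 days is an event and nobody else is, so regressing the first on the second separates perfectly whenever there is at least one event.

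**Listed assumptions.** A binary outcome has variance π(1 − π), which changes with the fitted probability π. Constant variance of the outcome is therefore not an assumption of the model. Proportionality belongs to hazard models and to ordinal logistic models, not to a binary logistic model.

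**The case against.** The strongest reply is that choice of estimator, event thresholds and predictor caps are often left to a separate analysis plan, which is not shown. That stands as far as it goes: not naming an estimator is no fault, and maximum likelihood is only the usual default. It does not excuse what section 6.13 does state, namely a predictor set as wide as the variable table, an outcome that is a cut of one of its own predictors, and two wrong assumptions.

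Several stronger readings are tempting, and the documents do not support them.

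- *All five outcomes are rare.* A rate is given for one only. It is a literature range under a 24-72 hour definition, whereas the trial uses 48 hours, and 25% is not rare. The true denominator is extubated patients, at most 74, so counts could be lower than those above.
- *The models will inevitably separate.* Near 25%, a model with arm alone or a few predictors almost never does. Joint entry of many predictors is permitted by the text but not stated.
- *About 20 false positives will appear* (5 outcomes × 80 variables × 0.05). This ignores the multiplicity adjustment promised in section 6.13. It also assumes 5% error per test, whereas Wald tests with sparse events reject less often than that.
- *The variance check must fail whenever a covariate matters.* Pearson residuals, named in the same sentence, are already divided by the fitted binomial standard deviation, so under a correct model their variance is constant. The listed assumption is wrong, but the planned residual check need not fail.
- *The secondary results rest on these models.* Fisher's exact test already covers the comparison between arms. Nor are the associations unplanned: finding factors associated with the secondary outcomes is a stated objective.

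**Conclusion.** The point holds as a minor correction to the regression models for binary outcomes. At the protocol's own background range, 74 patients give about 1.5 to 18.5 failed extubations, enough for at most about two parameters, against a variable list of about 80. Infinite or undefined arm odds ratios are likely at 2% (72%), a real risk at 5% (28%), uncommon at 10% (4%) and negligible at 25%, where the remaining problem is a wide interval. Models with many joint predictors are unstable at higher rates too. The perfect separation of prolonged ventilation on days of ventilation and the two misplaced assumptions stand whatever the rate.

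The figures assume equal rates in the arms, 37 analysed per arm, the literature range applied to the trial's outcome, and the 10-events rule of thumb. The simulated figures also assume unrelated predictors. For the other four outcomes no event count can be derived from the protocol. The primary analysis of ventilation time is not affected.

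**What to change.** In section 6.13, and in the matching text of section 1:

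1. For failed extubation and need for NIV, report the risk difference between arms with an exact or score 95% confidence interval, beside the Fisher test already planned.
2. If an odds ratio is wanted, use Firth-penalised logistic regression with arm and at most the randomisation strata (sex and age group), dropping to arm alone when events are few.
3. Limit the predictor models by the observed number of events, exclude any predictor that defines the outcome, and label these models exploratory.
4. Delete homogeneity of variance and proportionality of effects from the list of assumptions.

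The cost is a few lines of text and fewer exploratory associations. Sample size, data collection and the primary analysis do not change.

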|  | 
to the protocol and other relevant variables, to deepen the understanding of any joint influence that may affect the results. If statistically significant differences are not identified through the regression analyses, a post-hoc analysis will be carried out to evaluate whether the size of the recruited sample was adequate to detect possible differences between the established subgroups. This additional analysis will allow the interpretation of the results to be adjusted and will provide valuable information on the validity of the conclusions obtained.
 
Finally, an independent data monitoring committee will be established to conduct interim sample size reviews, allowing for adjustments based on variations in event rates observed during the study, thus ensuring adequate statistical power throughout the study.
 |
|--|------------------------------------------------------------------------------------------------------------------------------------------------------------------------------------------------------------------------------------------------------------------------------------------------------------------------------------------------------------------------------------------------------------------------------------------------------------------------------------------------------------------------------------------------------------------------------------------------------------------------------------------------------------------------------------------------------------------------------------------------------------------------------------------------------------------------------------------------------------------|

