#### 6.10. Follow-up and Safety Procedures

- **Lack of Significant Difference in the Duration of Mechanical Ventilation:** If at the end of the study and after analysis of the data, there is no statistically significant difference in the mean duration of mechanical ventilation between the early therapy group and the late therapy group, the trial could be considered a failure in terms of demonstrating the effectiveness of early therapy in reducing days on mechanical ventilation.
- **High Rates of Protocol Deviation:** If more than 20% of participants in one or both groups do not adequately comply with the study protocol, this could affect the validity of the results and lead to trial failure.
- **Safety Concerns or Unacceptable Toxicity:** If an unexpectedly high rate of serious adverse events is observed in the early versus late therapy group, the trial could be considered a failure due to safety concerns.
- **Low Participant Recruitment or Retention Rate.**
- **External Interference or Changes in Clinical Practice:** If significant changes in standard clinical practice occur during the study that affect the interpretation of the results, the trial could be considered a failure. For example, if a new treatment or procedure is introduced that impacts the duration of mechanical ventilation regardless of the therapy assigned in the trial.

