A detailed exploration will be conducted through a sensitivity analysis of possible interactions between identified subgroups, according to the RASS scale, protocol adherence, and other relevant variables, to deepen the understanding of any joint influence that may affect the study results. If no statistically significant differences are identified through regression analyses, a post-hoc analysis will be conducted to assess whether the recruited sample size was adequate to detect possible differences between the established subgroups. This additional analysis will allow adjusting the interpretation of the results and provide valuable information on the validity of the obtained conclusions.

Finally, an independent data monitoring committee will be established to conduct interim reviews of the sample size, allowing adjustments based on variations in event rates observed during the study, thus ensuring adequate statistical power throughout its execution.

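### After a null result, Section 6.13 runs a sample-size adequacy check with no stated effect size; on either natural reading it does not show which effects the data exclude

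*Protocol*

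**What the plan says.** Section 6.13 sets a condition, an analysis and a use for it.

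- Condition: "If no statistically significant differences are identified through regression analyses". It does not say which regressions are meant.
- Analysis: "a post-hoc analysis will be conducted to assess whether the recruited sample size was adequate to detect possible differences between the established subgroups".
- Use: "This additional analysis will allow adjusting the interpretation of the results and provide valuable information on the validity of the obtained conclusions".

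The Summary repeats the rule: "a post-hoc analysis will be carried out to evaluate whether the size of the recruited sample was adequate to detect possible differences", again for subgroup differences. Neither place names an effect size, a standard deviation or a threshold for adequacy.

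Two other places bear on it. Section 6.3 sizes the trial for the overall two-arm difference in days of ventilation and for nothing else. Section 6.10 deals with a null on the same outcome and says "the trial could be considered a failure in terms of demonstrating the effectiveness of early therapy in reducing days on mechanical ventilation", with no reference to a sample-size check.

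**The concern.** The rule works in one direction only. It runs after a null and never after a positive result, and its stated purpose is to change how that null is read. Its answer depends on an effect size that, as far as this protocol goes, is still open when the null is already known.

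The target is also displaced. The trigger is non-significance in unspecified regressions, which can include the primary Cox model, but adequacy is judged for differences between subgroups. That subgroups of a 74-patient trial are small is known before enrolment. It says nothing about whether the overall comparison was informative.

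What is at stake is the conclusion drawn from a null. A null is a realistic outcome: Section 4 cites a 750-patient trial of early mobilization that found no difference in days of ventilation. Readers would need to know which benefits this trial rules out.

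**Working it through.** **Inputs from the protocol.** Means 6.1 and 3.4 days (difference 2.7), SDs 1.4 and 1.25, stated alpha 0.05 and power 0.80 (Section 6.3); 37 per arm, 74 in total (Summary); 1:1 allocation (Section 6.4). **Assumptions of this review.** 60 to 74 extubation events, two subgroups of equal size, and SDs of 3 to 6 days as a range. The protocol gives none of these.

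**The plan's own figure.** The protocol gives no post-hoc or subgroup power. Its only related figure is 31 per arm (printed as 30.29). The printed formula with its substituted values gives 2(2.81 + 1.28)² × (1.40² + 1.25²) / 2.03² = 28.6. The stated alpha and power in the usual two-means formula give 2(1.96 + 0.842)² × 1.761 / 2.7² = 3.8, so 4 per arm. The figure of 31 is therefore not reproduced. That is a separate matter and the present point does not rest on it.

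**Reading 1: power at the observed effect.** With z the normal quantile for the observed two-sided p, power = Φ(z − 1.96) + Φ(−z − 1.96).

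| p | z | power |
|---|---|---|
| 0.05 | 1.960 | 50% |
| 0.10 | 1.645 | 38% |
| 0.20 | 1.282 | 25% |
| 0.50 | 0.674 | 10% |

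No quantity other than p enters. Every p above 0.05 gives less than 50%. The sample apparently needed for 80% power is ((1.96 + 0.842)/z)² times the actual one: 2.9 times at p = 0.10 and 7.3 times at p = 0.30.

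**Reading 2: power at the design effect.** Pooled SD = √((1.4² + 1.25²)/2) = 1.327. At 37 per arm the standard error is 1.327 × √(2/37) = 0.309, so power = Φ(2.7/0.309 − 1.96) = Φ(6.8), above 99.9%. At an assumed 7 per arm it is still 96.8%. The observed data do not enter, so the sample is called adequate whatever is found. If the SD is left to be chosen, the verdict moves with it: power for 2.7 days at 37 per arm is 97% with SD 3 and 49% with SD 6.

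**What an interval shows instead.** Suppose the observed difference is 0.5 days with 37 per arm.

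- SD 1.327: 0.5 ± 1.96 × 0.309 = −0.1 to 1.1 days. A 2.7-day benefit is excluded.
- SD 6: the standard error is 6 × √(2/37) = 1.395, giving 0.5 ± 2.73 = −2.2 to 3.2 days. A 2.7-day benefit is not excluded.

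Both results are non-significant. Reading 1 calls both underpowered (37% and 6%). Reading 2, at the protocol's SDs, calls both adequate. Only the interval separates them.

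**Precision on the hazard-ratio scale.** For the overall comparison the 95% interval is the estimate divided and multiplied by exp(1.96 × 2/√events): 1.58 at 74 events and 1.66 at 60. For an interaction between two equal subgroups the standard error doubles: exp(1.96 × 4/√74) = 2.5.

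**The case against.** A reader might infer that the check can only restate the p-value, that it will always blame the sample size, and that the trial could therefore never conclude that a large benefit is excluded. The protocol does not support that. It never says the observed effect will be used, and at its own design values the check gives the opposite answer. Section 6.10 allows a null to count as a failure to show effectiveness without any adequacy check, and nothing in Section 6.13 prevents a hazard ratio being reported with its interval.

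It can also be said that the choice of effect size is commonly left to a statistical analysis plan, that the sentence concerns subgroups and follows the one on subgroup interactions, and that no estimate or test changes. The first is fair as far as it goes. But the conditional rule and its use are stated here, and fixing the effect size later would only choose between two uninformative answers. On the second, the trigger is not limited to subgroup models, so an overall null can set it off. The third stands and limits the weight of the point: it affects interpretation only.

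**Conclusion.** The point holds as a defect in how a null will be interpreted. Section 6.13 and the Summary make an adequacy check conditional on non-significance and leave its effect size open. At the observed effect every null is called underpowered; at the protocol's 2.7 days and SDs the sample is called adequate regardless of the data. Neither shows which effects are excluded. Because the check addresses subgroup differences in a trial sized only for the overall comparison, an overall null could be discounted on irrelevant grounds, while Section 6.10 reads the same null as a possible failure and nothing says which reading governs.

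The power figures follow from the normal approximation and the protocol's own numbers. The hazard-ratio factors rest on assumed event counts, and the factor of 2.5 on two equal subgroups.

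**What to change.** Delete the post-hoc adequacy sentences in Section 6.13 and the Summary. Replace them with a rule that non-significant results are interpreted from the 95% confidence interval of the overall hazard ratio and of the difference in mean ventilation days. Read the latter against the 2.7-day design difference, or against another difference fixed before the data are seen. The protocol states no design hazard ratio, so the hazard-ratio interval has no reference value unless one is added. Since Section 6.13 may use a rank test for continuous variables, state that the difference in means and its interval are reported in either case, by bootstrap if needed. For subgroups, report the interaction ratio with its 95% interval, labelled exploratory. Refer to the same rule in Section 6.10 so that a null is read in one way.

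The cost is a few sentences in three places and the choice of a reference difference. No extra patients, visits or data are needed, and the hazard-ratio interval comes from the Cox model already planned.
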